## Abstract

Hip fractures are a major health concern, particularly for older adults, as they can reduce life quality, mobility loss, and even death. Current evidence reveals that early intervention is recommended for endurance in patients with hip fractures. To our knowledge, preoperative exercise intervention in patients with hip fractures remains poorly researched, and no study has yet applied aerobic exercise preoperatively. This study aims to investigate the short-term benefits of a supervised preoperative aerobic moderate-intensity interval training (MIIT) program and the added effect of an 8-week postoperative MIIT aerobic exercise program with a portable upper extremity cycle ergometer. The work-to-recovery ratio will be 1-to-1, consisting of 120 s for each bout and four and eight rounds for the pre- and postoperative programs, respectively. The preoperative program will be delivered twice a day. A parallel group, single-blinded, randomized controlled trial (RCT) was planned to be conducted with 58 patients each in the intervention and control groups. This study has two primary purposes. First, to study the effect of a preoperative aerobic exercise program with a portable upper extremity cycle ergometer on immediate postoperative mobility. Second, to investigate the additional effect of an 8-week postoperative aerobic exercise program with a portable upper extremity cycle ergometer on the walking distance at eight weeks after surgery. This study also has several secondary objectives, such as ameliorating surgical and keeping hemostatic balance throughout exercise. This study may expand our knowledge of preoperative exercise effectiveness in hip fracture patients and enhance the current literature about early intervention benefits.

## 1. Introduction

A hip fracture is the leading cause of morbidity in people 65 and older, ranking it in the top ten causes of person/year-adjusted disability for older adults [1]. In Greece, the majority of hospitalized patients with a hip fracture are over 75 years old [2]. Globally, the number of people with hip fractures is expected to increase significantly due to the aging population, and other factors, such as osteoporosis, partly attribute to insufficient physical activity [1]. In the US, according to data from the Centers for Disease Control and Prevention (CDC), one in three who practiced self-care before sustaining a hip fracture had to be institutionalized in a nursing home for at least one year after the fracture [3]. In Greece, between 1977 and 2007, hip fractures doubled, with the annual incidence rising to 343.96 per 100,000 inhabitants [4]. For the year 2019, Greece, in terms of the percentage of the population over 80, was in second place among the countries of Europe, with this age group constituting 7.1% of its total population. A prospective Greek cohort study documented an increased relative risk by 9% and 10% of 5- and 10-year mortality for each added year in age [5]. Evidence shows that patients with a hip fracture have a significantly higher risk of death up to one year after the fracture than those without a hip fracture. Up to 15 times higher mortality within one month after a hip fracture compared to non-fractured peers has been reported in the literature, not attributable to poor pre-fracture health status [1].

Many factors and biomarkers have been linked to survival and functional outcomes postoperatively in patients with hip fractures. For example, an elevated blood lactate concentration has been implicated in increased immediate or mid-term postoperative mortality during surgery [6]. Similarly, decreased albumin levels are a strong independent predictor of mortality after a hip fracture, and prealbumin also appears to be an important marker due to its better sensitivity to changes [7]. Examining in a Bayesian Belief Network structure the predictors’ survival 1 year after hip fracture surgery, the number of comorbidities on admission (≥2 conditions) and levels of nitrogen (≥9 mmol/L), albumin (<35 g/L) and lactate (≥2 mmol/L) in the blood, are the four first-rate predictors of survival [8]. Moreover, venous thrombosis remains one of the main reasons for readmission to the hospital in the first 30 days after surgery [9]. Blood coagulation involves complex pathways which regulation depends on several factors. There is clear evidence that hip fractures are associated with blood hypercoagulability, and pharmaceutical and mechanical prophylaxis is necessary [10,11,12,13]. Finally, delayed surgery has been associated in many observational studies with increased mortality and serious complications [14].

People recovering from a hip fracture are also at a high risk of muscle weakness and fear of falling and experience limitations in mobility, self-care, and participation in the community [1]. These consequences last months after surgery, with 50% experiencing reduced functionality within one year, while only 30% regain full functionality [15]. Exercise has significant benefits for several of these variables, such as the level of independence and self-care [16,17], the faster clearance of accumulated lactate [18,19], the increased activity of pyruvate dehydrogenase [20] and the immediate enhancement of cognitive functions [21]. Hemostasis is also linked to exercise physiology, as it affects blood coagulation, fibrinolysis and platelets [22]. It has been shown that exercise promotes fibrinolysis, with increased levels of tissue plasminogen activator (t-PA), decreased fibrinogen and decreased plasminogen activator inhibitor (PAI-1). Furthermore, following specific exercise protocols has been shown to decrease surrogate markers of thrombin and endogenous thrombin potential (ETP) [23,24,25]. Regular aerobic exercise is associated with a decreased resting platelet aggregation and activation and thrombomodulin for platelet function, and there is an indication of a reduced thrombin–antithrombin complex [26]. The observed exercise-induced changes in the coagulation factors occur independently of the older adult’s lipid profile, aerobic capacity and body composition [27].

In a recent umbrella review, early intervention seems to be beneficial for improving the endurance in hip fracture patients [28]. However, it is not yet clear if early intervention has any effect on functioning, quality of life, length of stay and mortality in this specific population. In order to prevent mortality and morbidity, preoperative physical therapy programs have been implemented in various conditions, such as in cardiac operations [29], in non-small cell lung cancer [30] and in major abdominal surgery [31], as well as in various other orthopedic surgeries (e.g., knee and hip arthroplasty) [32]. To the best of our knowledge, preoperative physical therapy intervention in patients with hip fractures remains poorly researched, and no study was found in the literature with the application of aerobic exercise preoperatively. The study aims to investigate the short-term benefits of a preoperative aerobic exercise program and the added effect of an 8-week postoperative aerobic exercise program with a portable upper extremity cycle ergometer.

## 2. Materials and Methods

### 2.1. Study Design

The study protocol has been prospectively registered in the open database for study protocols, ClinialTrials.gov (registration number: NCT05389800) [33]. The study received approval number 402/26-7-2021 from the Institutional Review Board of the “Attikon” University Hospital (1st Department of Orthopaedic Surgery, National and Kapodistrian University of Athens) 7 September 2021.

A parallel group, single-blinded, randomized controlled trial (RCT) will be conducted with two groups of hip fracture patients. The sample will be recruited from a tertiary University Hospital (1st Department of Orthopaedic Surgery, “Attikon” University Hospital, Athens, Greece). The randomization will be done at the time of admission of the patients to the emergency department (ED) and after their written informed consent form. The study protocol’s instructions will be described through an informed consent form in plain language, along with all the procedures the subjects will undergo and the risks and benefits of participation. Allocation concealment will be ensured by using sequentially numbered, opaque, sealed envelopes. The envelopes were created by a biostatistician, who will participate actively in neither the delivery of any intervention nor in the outcome measures assessment. For the preoperative program, 116 patients need to be recruited, who will be randomized with a ratio of 1:1 using the block randomization method (58 in the intervention group and 58 in the control group). Immediately after the surgery, the participants of each group will continue in the postoperative intervention program: the intervention group (IG) will continue with the exercise program three times a week for a total of 8 weeks, while the control group (CG) will not receive any intervention at any time point after surgery (Figure 1, graphic illustration).

### 2.2. Implementation of the Study

#### 2.2.1. Getting Informed Consent

Participants will be informed of the purpose of the study, and their signed consent will be requested at the start of the study after it has been ensured that they meet the inclusion criteria and do not meet any of the exclusion criteria. Participation in the study is voluntary, and participants may discontinue participation at any time.

#### 2.2.2. Regulatory Study Approval

The present study is an interventional study that is not subject to government decision D3(a)—36809 (Government Gazette B 2015, 3-6-2019); therefore, it has not been submitted to the National Medicines Agency (ΕOΤ), and an approval from the ethics committee is sufficient and ethics of the center/body conducting the study. The present study has been designed following the rules of research ethics and ethics resulting from the Declaration of Helsinki.

#### 2.2.3. Final Report and Publications

A final report with study results will be prepared after this research study. Publications will comply with the International Committee of Medical Journal Editors (ICMJE) guidelines. Negative and positive results should be published or made available publicly. Regarding authors, the following criteria should be met:Authors must make substantial contributions to study the conception and design, data acquisition or data analysis and interpretation of the results.Authors must draft the article for publication or, during authorship review, contribute (data analysis, interpretation or other important intellectual content) to the extent that leads to a significant revision of the article in agreement with the other authors.Authors must provide written approval of the article’s final version before submission.

### 2.3. Participants

The study will include both male and female participants, making the research more representative and diverse. All participants will be 65 years and older, highlighting a focus on the geriatric population who more regularly suffer hip fractures due to falls. The study will specifically target individuals undergoing surgery for hip fractures, providing valuable insights into the management and outcomes of this patient population. A total of 116 patients will be enrolled in the study, with 58 patients assigned to each group, namely the intervention and control groups. This equal allocation ensures a balanced comparison of the outcomes between the two groups.

### 2.4. Eligibility Criteria

Of the patients hospitalized at the 1st Department of Orthopaedic Surgery in the “Attikon” University Hospital (Athens, Greece), candidates to participate in the study will meet all of the following inclusion criteria and not meet any of the exclusion criteria. To mitigate attrition, the exercise program will be individualized, and there will be regular follow-up assessments. The postoperative exercise program will also be delivered at home; thus, it will be easier for patients to engage in it as planned. Patients will not receive any fee for participating in the study.

#### 2.4.1. Inclusion Criteria

Age: 65 years old and olderUnilateral proximal femoral fracture/hip fracture (intertrochanteric or neck fracture)Ambulatory patients before fracture (with or without aid assistance), according to their New Mobility Score (NMS)Absence of any severe neuropsychiatric disorder (e.g., severe psychiatric disorder or dementia) to the extent that the researcher deems the patient incompetent or likely unable to remain compliant with the follow-up. All patients will be tested with Addenbrooke’s Cognitive Test III (ACE-III) to exclude those with moderate or severe dementia (<61 in total score) [27]Agreed to participate and signed the informed consent form

#### 2.4.2. Exclusion Criteria

Pathological fractures (on the ground of malignant musculoskeletal tumor)Unable to implement the exercise program due to underlying pathology or disability in the upper extremitiesMore than one fractureUnderlying avascular necrosisSevere and unstable cardiovascular disease (e.g., congenital heart disease, severe uncontrolled hypertension (systolic blood pressure ≥180 mmHg or diastolic blood pressure ≥120 mmHg) or unstable angina)Neurological or other conditions that significantly impair function and independence (e.g., stages 3–5 Parkinson’s disease based on the Hoehn and Yahr scale, advanced multiple sclerosis or severe osteoarthritis of degenerative or rheumatic etiology)Severe metabolic bone disease (e.g., Paget’s disease, renal bone disease or osteomalacia), excluding osteoporosisAny aggressive end-of-life disease (e.g., end-stage cancer with an estimated survival expectancy of less than six months)Unable to understand the informed consent form and protocol instructionsRefusal to participate in the research

#### 2.4.3. Withdrawal Criteria

Inability to participate in the inpatient program for more than two consecutive days (e.g., due to fever or early surgery within two days) or abstinence from more than 20% of the scheduled sessions in the postoperative programIntense subjective discomfort during exercise or development of other severe symptomatology or signs, as described in Section 2.4. Safety considerations and handling of adverse eventsPatient’s choice to drop out of the program

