After each session, the lactate concentration of the capillary blood will be collected via a hand-held lactate analyzer (Lactate Scout 4, EKF Diagnostics, Leipzig, Germany), and the aim will be to maintain the capillary blood lactate concentration up to 2.0 mmol/L (±0.5).

The postoperative program will be performed initially in the hospital and at home after discharge. It will consist of 120 s of moderate-intensity exercise and 120 s of passive rest for eight cycles. The basic program will last about 30 min, not including warm-up and cool-down. An additional 5 min in total is calculated for warm-up and recovery. The program will be performed three times a week for eight weeks. The adaptation of the exercise intensity will be regulated by modifying the external load (watts) to keep the internal load of moderate intensity (64–76% HRmax, 12–13 in RPE). For the postoperative program, individuals will be allowed to follow the standard care, such as physical therapy sessions added to aerobic exercise. Standard care refers to postoperative rehabilitation. Such intervention will not be a part of our study’s protocol, and we will not intervene in patients’ decision to participate in physiotherapy sessions. These sessions will not be delivered by the research team, but it will be mentioned if they were conducted.

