#### Attention Control Group

The control group will participate in a program of memory and attention activities of very low intensity with upper extremity movements using an interactive platform (Kinesthetic Multi-Sensory Games, Kinems, Greece). To maintain equal attention time with the intervention group, the program will last 20 min. There will be a simultaneous recording of the HR, while the RPE scale will be evaluated at the end of each session. For the postoperative program, no intervention will be performed beyond the standard care, such as physical therapy sessions without aerobic exercise.

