### 2.6. Safety Considerations and Handling of Adverse Events

The inpatient and home exercise programs will be implemented and supervised by health professionals certified in first aid. Any intervention out of the hospital will begin after a cardiac clearance of the patient. For participating in the pre- and postoperative exercise program, approval by the attending orthopedic physician will be a prerequisite. During the initial assessment for planning and for any individualized modification to the planned exercise program to minimize potential adverse effects, the therapist will consider the following: current medical condition; medical history; comorbidities (e.g., diabetes and hypertension); medication (including dosage and time of administration); relevant clinical data (e.g., resting blood pressure and HR and oxygen saturation); instructions and cautions from other healthcare professionals; past and recent physical activity level time before the fracture and other factors that may affect exercise prescription (e.g., another injury).

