#### 2.6.1. Absolute Contraindications for Exercise [35,36,37]

Progressive worsening of exercise tolerance or dyspnea at rest over previous 3–5 daysPresence of critical narrowing of the left coronary artery (obstructive left main coronary disease)Unstable anginaUncontrolled cardiac arrhythmiaAcute endocarditis, myocarditis or pericarditisModerate to severe aortic stenosisDecompensated heart failureAcute pulmonary embolism or deep-vein thromboembolismAortic dissectionHigh-grade atrioventricular blockHypertrophic obstructive cardiomyopathyRecent cerebrovascular accident (CVA) or transient ischemic attackUncontrolled diabetesRetinopathySevere autonomic or peripheral neuropathyAcute systemic illness or feverAcute or chronic renal failurePulmonary fibrosis or interstitial lung diseaseRecent myocardial infarction (<4 weeks), coronary artery bypass grafting (<4 weeks) or percutaneous coronary intervention

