## 3. Discussion

This study has two primary purposes. First, to study the effect of a preoperative aerobic exercise program with a portable upper extremity cycle ergometer on immediate postoperative mobility. Second, to investigate the additional effect of an 8-week postoperative aerobic exercise program with a portable upper extremity cycle ergometer on the walking distance at 8 weeks after surgery. This study also has a number of secondary objectives. Regarding the preoperative exercise program evaluation of the effect of the preoperative program on surgical stress (via blood lactate levels), perioperative bleeding and transfusion requirements, hemostasis factors will be evaluated, in addition to, an evaluation of the effect of the postoperative program in the short and long term: lower extremity functionality, aerobic capacity, nutritional status, hemostasis factors, mortality, rehospitalization and complications related to surgery and hospitalization (thrombotic and thromboembolic events).

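### The 20% missed-session withdrawal rule can reach only the exercise arm; if withdrawn patients leave the 8-week assessment or analysis, the primary 6MWT comparison loses the protection of randomisation

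*Protocol article*

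**What the plan says.** Section 2.4.3 (Withdrawal Criteria) includes "abstinence from more than 20% of the scheduled sessions in the postoperative" programme and names no arm.

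The schedule for the exercise arm is in 2.5: "The program will be performed three times a week for eight weeks". For the other arm, 2.1 says that "the control group (CG) will not receive any intervention at any time point after surgery", and the control-group paragraph agrees: "For the postoperative program, no intervention will be performed beyond the standard care". Ordinary physiotherapy is open to both arms but lies outside the protocol. Section 2.5 says of it: "These sessions will not be delivered by the research team".

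The Discussion gives as the second primary purpose the effect of the postoperative programme "on the walking distance at 8 weeks after surgery". Section 2.8.1 sizes the trial on that outcome and raises the sample by 20% for losses. Among the causes of loss it lists comorbidities that force the programme to stop and patients who choose to stop it. Section 2.8.2 plans a t-test or Mann–Whitney comparison of the two groups. No section says whether a patient withdrawn under 2.4.3 still attends the 8-week 6MWT.

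**The concern.** The rule acts after randomisation and depends on behaviour that can be observed in one arm only. An exercise patient who misses five sessions meets a withdrawal criterion. A control patient in the same condition has no sessions to miss and stays in.

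If withdrawal means loss from the 8-week walk test or from its analysis, the exercise arm is reduced to its better attenders and compared with a control arm not filtered in that way. Should attendance and walking ability go together, a difference would appear even if the exercise did nothing. An analysis plan that is not shown could call for analysis as randomised, but it could not recover walk tests that were never done.

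**Working it through.** **1. Who can meet the rule.** Exercise arm: 3 sessions × 8 weeks = 24 scheduled. 20% of 24 = 4.8, so more than 20% means 5 or more missed. Control arm: 0 scheduled postoperative sessions, and outside physiotherapy is not part of the programme. The clause therefore cannot be met in the control arm. This applies to the 20% postoperative clause. The inpatient clause of 2.4.3 and the patient's own choice to stop can apply to both arms.

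**2. The plan's own figure.** Inputs from 2.8.1: difference 50 m, SD 75 m, α = 0.05 (sidedness not stated; two-sided assumed), power 90%, ratio 1:1.

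n per arm = 2 × (1.960 + 1.282)² × 75² / 50² = 47.3, rounded up to 48, so 96 in total, as stated. Then 96 × 1.2 = 115.2, rounded up to an even 116, or 58 per arm, as stated. The figures reproduce, so the issue is selection and not sample size.

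**3. Size if withdrawn patients are left out.** The document gives neither a withdrawal rate nor a correlation, so both are assumptions:
- q = share of the exercise arm withdrawn, taken to be its least adherent patients;
- ρ = correlation between attendance and 8-week 6MWT;
- the two are bivariate normal, there is no true effect, and all 58 controls are kept.

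With λ = φ(z_q)/(1 − q):
- bias = ρ × 75 × λ;
- standard error = 75 × √(v/[58(1 − q)] + 1/58), where v = 1 − ρ²λ(λ − z_q);
- type I error = P(|Z + bias/SE| > 1.96), by normal approximation.

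λ = 0.195, 0.350 and 0.497 for q = 10%, 20% and 30%.

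| q (patients of 58) | ρ = 0 | ρ = 0.2 | ρ = 0.3 | ρ = 0.5 |
|---|---|---|---|---|
| 10% (5.8) | 0 m; 5% | 2.9 m; 5.5% | 4.4 m; 6.1% | 7.3 m; 8.2% |
| 20% (11.6) | 0 m; 5% | 5.2 m; 6.5% | 7.9 m; 8.4% | 13.1 m; 15.0% |
| 30% (17.4) | 0 m; 5% | 7.5 m; 7.8% | 11.2 m; 11.4% | 18.6 m; 24.3% |

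The largest entry is 18.6/50 = 37% of the target difference.

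**4. If controls are lost too.** Suppose the same mechanism removes 20% of the exercise arm and 10% of controls (also an assumption). The net bias is 7.9 − 4.4 = 3.5 m at ρ = 0.3, and 13.1 − 7.3 = 5.8 m at ρ = 0.5.

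**5. If nobody is left out.** When all randomised patients are assessed and analysed whatever their attendance, this rule causes no selection bias. Power at 58 per arm is about 95%.

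**The case against.** **Withdrawal may mean leaving the programme only.** The last item of 2.4.3 speaks of dropping out of the programme, so the whole list can be read as rules for stopping exercise, with assessment continuing. The article names no analysis set, which a full protocol or analysis plan commonly does, so that silence proves nothing. A reader might infer that the 8-week comparison is biased as a matter of fact, but the document does not support that. What remains is that the section is headed as withdrawal, 2.8.1 counts stopping the programme as drop-out, and nothing keeps these patients in follow-up.

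**Direction is assumed.** The Discussion names lack of interest in exercise as the main reason why older adults do not take part, so poor attendance is not simply frailty. At ρ = 0 there is no bias. Frail controls may also die or fail to reach the assessment, which shrinks the imbalance. Both points stand. Section 2.8.1 does, however, name comorbidities among the reasons for stopping, so a positive correlation is plausible.

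**How many would be withdrawn.** It is tempting to assume an attendance rate and derive the share withdrawn from a binomial model with independent sessions. Under one common rate with independent sessions, who is withdrawn is chance and the bias is zero, so that model cannot be joined to the selection calculation above. The share is better left as an open assumption.

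**A second one-sided filter.** Section 2.6 states "For participating in the pre- and postoperative exercise program, approval by the attending orthopedic physician will be a prerequisite", and 2.6.1 lists "Absolute Contraindications for Exercise", several of which (retinopathy, renal failure, uncontrolled diabetes) are not evidently covered by 2.4.2. A reader might infer that such patients are randomised, then removed from the exercise arm and kept as controls. The document does not say that the list is first checked after randomisation, nor that a contraindicated patient is withdrawn. The cardiovascular and neurological exclusions in 2.4.2 are open lists that may cover part of it. This supports a request to reconcile the sections and no more.

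**Conclusion.** The concern holds in conditional form. That the 20% clause reaches one arm only follows directly from 2.1, 2.4.3 and 2.5. That it distorts the primary 8-week 6MWT comparison depends on withdrawn patients leaving the assessment or analysis, which is the more natural reading but is not stated outright. On that reading the comparison is no longer protected by randomisation.

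The error probably favours exercise, provided that poor attenders walk less far. The documents cannot fix its size. Over the assumed ranges (10–30% withdrawn in the exercise arm only, ρ from 0 to 0.5) it runs from nothing to about 19 m and from a 5% to about a 24% false-positive rate. It matters because walk tests not done at eight weeks cannot be supplied later.

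**What to change.** Reword 2.4.3 so that missed sessions and exercise-stopping events mean discontinuation of the exercise programme, not withdrawal from the study. State that these patients stay in all scheduled assessments unless they withdraw consent, and that all patients are analysed in the arm to which they were randomised. Use the 20% threshold only to define a per-protocol sensitivity analysis; 2.5 already provides for recording adherence.

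Separately, reconcile the exclusion criteria in 2.4.2 with the contraindications and approvals in 2.6 and 2.6.1, and state when these are checked relative to randomisation. Which conditions should exclude a patient is a clinical matter for the sponsor.

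The cost is small: protocol wording, visits that are already scheduled, and no change to the sample size of 116. The estimated effect may be somewhat smaller because patients who stopped exercising are counted.

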#### 2.7.2. Aerobic Capacity

The distance covered with the 6-minute walking test (6MWT) will be evaluated to assess their aerobic capacity. The 6MWT is an easy-to-use and reliable functional capacity assessment test. It is widely used and considered ideal for patients with respiratory, cardiovascular and other diseases characterized by reduced physical fitness [44,45]. It is simple to perform, easily understood by patients and reflects patients’ ability to cope with their daily activities, which mostly require submaximal work. The distance covered during the 6-minute walking test has been found to be positively correlated with the VO_2_ peak [46].

Patients are asked to walk as far as possible for 6 min. The patient will be allowed to use an external aid. There is strong evidence for the reliability and validity of the test in patients after hip fractures. Overgaard et al. [47] reported minimum detectable changes (MDC) without aid at 59.4 m and with aid at 49.8 m. The test will be performed along a 25 m aisle, and the HR will be simultaneously recorded using a HR monitor chest strap (Polar H10, Polar Electro, Kempele, Finland). The assessment will be performed at 4, 8, 26 and 52 weeks postoperatively.

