However, based on the study by Karagiannis et al. [5] on a Greek population, mortality at six months after a fracture is 10.5%. However, both because this particular study reports a lower incidence of mortality at 6 and 12 months postoperatively compared to studies in other countries [57], and because of other factors that will likely contribute to the drop-out rate, such as comorbidities that will lead to the mandatory interruption of the program or the patient’s desire to interrupt the program for personal reasons, an increase in the sample size by 20% is deemed necessary, with the result that the sample size is set at 116 people (intervention group n1 = 58, control group n2 = 58).

Considering the above, in order to ensure the necessary power to investigate both primary purposes, the sample size is set at 116 subjects.

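### Exercise intolerance is a withdrawal criterion that, after surgery, study exercise can trigger in one arm only, so the week-8 6MWT may lose the least tolerant exercisers

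*Protocol article*

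**What the plan says.** Section 2.4.3 (Withdrawal Criteria) of the protocol article lists intense "subjective discomfort during exercise or development of other severe symptomatology or signs, as described in Section 2.4. Safety considerations". Its first item also withdraws a patient for "abstinence from more than 20% of the scheduled sessions in the postoperative" programme.

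After surgery the two arms differ in exposure. For the intervention group, section 2.5 says: "The program will be performed three times a week for eight weeks". For controls, section 2.1 says that "the control group (CG) will not receive any intervention at any time point after surgery", and the Attention Control Group text says that "no intervention will be performed beyond the standard care". Section 2.5 adds that standard-care physiotherapy lies outside the study protocol and is not delivered by the research team.

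The second primary purpose concerns walking distance at 8 weeks. For the 6MWT, section 2.7.2 says: "The assessment will be performed at 4, 8, 26 and 52 weeks postoperatively".

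Section 2.8.1 names "comorbidities that will lead to the mandatory interruption of the program" among the reasons for drop-out, and concludes that "an increase in the sample size by 20% is deemed necessary", which takes the total from 96 to 116.

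**The concern.** After surgery, discomfort during study exercise can arise only where there is study exercise, so this trigger works in one arm. The other half of the item, severe symptoms or signs, could also reach controls, so the asymmetry is clear only for the exercise trigger.

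Patients who cannot tolerate moderate arm exercise are plausibly the frailer ones, who walk less far. If they leave the exercise arm while equally frail controls stay, the comparison favours exercise on a primary outcome even when the programme does nothing. The 20% increase in sample size protects power but does not correct selective loss in one arm.

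The 3-day Cumulated Ambulation Score is less exposed, because few sessions precede it and controls also have study sessions before surgery.

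**Working it through.** **The plan's own figure.** Section 2.8.1 assumes 250 v 300 m, SD 75 m, α = 0.05 and 90% power. Taking α as two-sided:

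- n per arm = 2 × (1.96 + 1.2816)² × 75² / 50² = 47.3, so 48 per arm and 96 in total, as stated.
- 48 × 1.2 = 57.6, so 58 per arm and 116 in total, as stated.

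**How the two withdrawal rules interact.** The postoperative programme has 3 × 8 = 24 sessions. Twenty per cent is 4.8, so missing 5 breaches the limit. A patient stopped for intolerance after 24 − 5 = 19 or fewer sessions (up to the first session of week 7) must miss at least 5. That patient then meets the missed-session criterion as well, so changing the intolerance item alone would not keep the patient in the trial.

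**Size of the bias.** The documents give neither a withdrawal rate nor the correlation between tolerance and 6MWT. The assumptions are:

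- true effect zero;
- SD 75 m (section 2.8.1) and 58 randomised per arm;
- correlation r between exercise tolerance and 6MWT;
- the k least tolerant exercisers and the m least tolerant controls are lost.

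The mean of an arm that loses j of 58 shifts upward by r × 75 × φ(z_d) / (1 − d). Here d = j/58, z_d is the d-quantile of the standard normal and φ its density. The bias is shift(k) − shift(m).

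Example for k = 5, m = 0, r = 0.5: d = 0.0862, z_d = −1.364, φ = 0.1573, and 0.1573/0.9138 = 0.1721. The shift is 0.5 × 75 × 0.1721 = 6.5 m.

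The standard error is 75 × √(1/(58 − k) + 1/(58 − m)), about 14.1 to 14.4 m. The chance of a false result favouring exercise is 1 − Φ(1.96 − bias/SE), nominally 2.5%. The two-sided error adds the opposite tail, Φ(−1.96 − bias/SE).

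| Exercisers lost / controls lost | Bias at r = 0.3 / 0.5 / 0.7 (m) | False result favouring exercise, r = 0.5 | Two-sided error, r = 0.5 |
|---|---|---|---|
| 2 / 0 | 1.8 / 3.0 / 4.2 | 4.0% | 5.5% |
| 5 / 0 | 3.9 / 6.5 / 9.0 | 6.6% | 7.4% |
| 2 / 1 | 0.8 / 1.3 / 1.9 | 3.1% | 5.1% |
| 5 / 2 | 2.1 / 3.5 / 4.9 | 4.3% | 5.7% |

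Equal losses under the same selection give zero bias. A simulation of 40,000 trials at r = 0.5 gave biases of 3.0, 6.3, 1.3 and 3.5 m, and favourable-error rates of 4.2%, 6.8%, 3.4% and 4.5%, in the same order.

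As a share of the planned 50 m, the first two rows at r = 0.5 are 3.0/50 = 6% and 6.5/50 = 13%.

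**The case against.** **The loss is inferred.** No sentence says that a patient who meets section 2.4.3 misses the week-8 walk. The third item of that list speaks of leaving the programme, and section 2.6.2 is headed as temporary cessation, so withdrawal could mean stopping exercise only. The sample-size text is an allowance and does not name exercise discomfort. This stands as a caution, and the claim is therefore that patients may be lost. But the protocol does not separate stopping exercise from leaving the study, and its planning treats programme interruption as drop-out for this endpoint.

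**A condensed article leaves analysis sets and follow-up rules to other documents.** That is fair for analysis sets. The point here is a stated conduct rule: it decides who is withdrawn, and following it as written can produce the selective loss.

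**Safeguards make intolerance uncommon.** Unstable cardiovascular disease and upper-limb disability are excluded. Physician approval is needed, cardiac clearance precedes exercise outside hospital, and load is adjusted to perceived exertion. These lower the likely number of such withdrawals but leave the one-arm trigger in place.

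**The magnitude is assumed, and the favourable tail looks worse than the total error.** Both are true. The two-sided error at r = 0.5 is only 5.1% to 7.4% in the cases shown, and no passage links tolerance of arm cranking to walking distance.

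**A week-4 walk exists.** For patients stopped after that visit, an analysis could use it to model the missing value. This softens the loss, but a week-4 value does not replace an unmeasured week-8 walk.

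**The missed-session rule is the stronger trigger.** It is explicit and countable, and it catches most of the same patients. That is a reason to change both rules together.

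**Conclusion.** The concern holds at moderate strength. As written, section 2.4.3 can selectively remove intolerant patients from the exercise arm before the week-8 6MWT, in a direction that plausibly favours exercise. That rests on two inferences: that withdrawal ends assessment, which section 2.8.1 implies but does not state, and that tolerance is related to walking distance.

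The effect is probably small: a few metres against 50 m in the cases examined, less if controls also lose frail patients, and nil if losses match. It is worth correcting because it touches a primary outcome and an unmeasured walk cannot be recovered at analysis.

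**What to change.** Amend section 2.4.3 so that the intolerance criterion and the missed-session criterion both end study exercise only. Treat the two-day inpatient rule the same way when the absence follows such a stop. State that the 6MWT and all other scheduled assessments continue unless the patient withdraws consent, and that patients are analysed in their allocated arm.

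In the same edit, correct the cross-reference: safety considerations are in section 2.6, not 2.4. Section 2.6.2 should also say which signs pause a session and which end study exercise.

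The cost is a wording amendment, a short staff briefing and minor extra follow-up at visits already scheduled. The statistical cost is some dilution. If k retained exercisers gain nothing, the planned difference becomes 50 × 48/(48 + k): 48.0 m for k = 2 and 45.3 m for k = 5. With 48 + k exercisers and 48 controls, power is 88.6% or 85.8%, against 90.4% for 48 per arm at 50 m.
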